### Participant timeline {13}

All assessments (filling out electronic forms, videoconferencing and EMA) will be made via the internet or by telephone. Figure 1 shows the instruments and the time points at which they will be used.

**Fig. 1 Fig1:**
[figure not shown]
Schedule of enrolment, interventions and assessments. ARI: Affective Reactivity Index; CGAS: Children’s Global Assessment Scale; CGI-I: Clinical Global Impression-Improvement; CGI-S: Clinical Global Impression-Severity; DASS-21: 21-item Depression, Anxiety and Stress Scale; EMA: Ecological momentary assessment; MFQ-SI: Mood and Feelings Questionnaire-Suicidal Ideation; PedsQL: Pediatric Quality of Life Inventory; RCADS-25-C: 25-item version of the Revised Children’s Anxiety and Depression Scale, child report; RCADS-25-P: 25-item version of the Revised Children’s Anxiety and Depression Scale, parent report; SDQ: Strengths and Difficulties Questionnaire; TSQ: Telemedicine Satisfaction Questionnaire

Parents will complete an online form for eligibility screening and for the collection of sociodemographic data, as well as the 21-item parent-report psychopathology questionnaire Depression, Anxiety and Stress Scale (DASS-21) [50]. If their child/adolescent is considered eligible in this first assessment, a videoconference with a blinded outcome assessor will be scheduled. In this first videoconference, the eligibility criteria will be checked with the guardian and the child/adolescent. The baseline (T0) assessment will be made, confirming or correcting clinical data previously reported by the guardian at the eligibility screening. Two other videoconferences, in which similar clinical data will be collected by the blinded outcome assessor, will be scheduled for T1 and T2.

As previously mentioned, active smartphone data collection (the EMA) will be performed in the week prior to the intervention and in the week after its end, whereas passive smartphone data collection (through the pRMT application) will take place from T0 to T2. At T1, guardians in the intervention group will be asked to complete an online form comprising an adapted version of the TSQ [48].

### Sample size {14}

In a meta-analysis, Vigerland et al. [51] found the estimated size-effect for internet-delivered CBT in children and adolescents to be 0.62 (95% CI 0.41–0.84). Given that most of the studies assessed in that meta-analysis evaluated interventions involving a greater number of sessions than that to be evaluated in our study, we decided to be conservative and expect an effect size within the lower bound of that confidence interval, that is, 0.41. Therefore, the minimum sample size would be 190 participants, with an alpha of 0.05, power of 80% and 1:1 randomisation. Assuming an estimated attrition rate of 30%, we will need a total sample of 280 participants.

### Recruitment {15}

The study will be promoted via social media and email campaigns. People residing anywhere in Brazil will be able to participate. Parents interested in participating in the study will be referred to the study website, where they will be provided with further information regarding the study and the inclusion/exclusion criteria. They will then be asked to complete a basic online screening form and, if they meet the initial criteria, will be invited to a baseline assessment to be conducted through videoconference, in which the inclusion and exclusion criteria will also be confirmed.

## Assignment of interventions: allocation

### Sequence generation {16a}

Randomisation will occur in real time, via a computer algorithm created to minimise differences between the two groups regarding sex and age, the latter being dichotomized as 8–11 years (children) or 12–17 years (adolescents). This algorithm uses the Aitchison distance to stratify the groups according to the chosen parameters [52], as has been done in previous studies [53–55].

### Concealment mechanism {16b}

Participants meeting the inclusion and exclusion criteria will be listed sequentially by a research manager in a spreadsheet that will be used by another research manager for the randomisation. The latter research manager will have no direct contact with the patients.

### Implementation {16c}

A research manager will randomise the patients using the computer algorithm described above. Another manager will then assign the participant to the respective intervention group, in accordance with the result of the randomisation.

## Assignment of interventions: blinding

### Who will be blinded {17a}

The outcome assessor will be blinded to the group allocation. Families will be instructed not to provide the outcome assessor with any details regarding the treatment.

### Procedure for unblinding if needed {17b}

The design of the trial is single-blind. Because only the outcome assessors will be blinded, no unblinding will occur.

## Data collection and management

### Plans for assessment and collection of outcomes {18a}

All assessors will be clinical psychologists with previous experience in child and adolescent mental health who have been trained in the study protocol by the study team coordinators. The instruments used in the assessments are described below.Sociodemographic questionnaire—the guardian will complete an online form designed to collect data on socioeconomic status, level of education, occupation and income, as well as data such as the age/sex of the child/adolescent, COVID-19 exposure history and routines (including study hours, sleep habits, sleep quality and screen time). Sleep quality will be assessed with an adapted version of the Single-item Sleep Quality Scale, which is comparable to other sleep scales such as the Pittsburgh Sleep Quality Index [56]. Guardians will rate the sleep quality of their child/adolescent according to a 5-point Likert scale ranging from 0 (“terrible”) to 4 (“excellent”).DASS-21 [50]—The DASS-21 is a 21-item scale covering internalising symptoms in depression, anxiety and stress domains over the last 2 weeks. It consists of 21 statements (e.g. “I found it hard to wind down”) that will be scored by the guardians using a 4-point Likert scale ranging from 0 (“did not apply to me at all”) to 3 (“applied to me very much or most of the time”). It has been shown to possess adequate validity and reliability in the Brazilian population (Cronbach’s alpha: 0.92 for the depression subscale; 0.90 for the stress subscale; and 0.86 for the anxiety subscale) [57].RCADS-25—The RCADS-25 is a shortened version of the Revised Child Anxiety and Depression Scale. The original scale has 47 items and has been shown to be appropriate for use in various cultures, including that of Brazil [58]. The 25-item version is comparable to the original scale, and its use is preferred to reduce the burden of the respondent [30]. As previously mentioned, we will apply the RCADS-25-P and RCADS-25-C [28, 29]. In a clinical sample, the alpha coefficients for the RCADS-25-C depression and anxiety scales were 0.80 and 0.91, respectively, whereas they were 0.79 and 0.76, respectively, in a community sample [29]. For the RCADS-25-P, the reported alpha coefficients were 0.83 for the depression scale, 0.85 for the anxiety scale and 0.85 for the total scale [28].MFQ-SI [31, 32]—The original MFQ is a 33-item questionnaire on mood symptomatology that has been adapted for use in Brazil [59]. Guardians will answer only the questions on the four-item composite version related to suicidal ideation (MFQ-SI), a topic that is not covered on the RCADS-25.PedsQL—The PedsQL family impact module is a 36-item parent-report questionnaire that aims to assess the impact of chronic medical conditions on the quality of life of the family [49]. It has been adapted for use in Brazil [60]. We will use its five-item family relationships subscale to assess family dynamics. The subscale employs a 5-point Likert scale with responses ranging from “never” to “almost always” on topics such as “lack of communication between people in my family”.SDQ—The original SDQ is a 25-item questionnaire on child and adolescent psychopathology that has been adapted to many languages and used extensively in various countries, including Brazil [43], in its informant-report and self-report forms. There is an extended version of the SDQ [61] that includes a brief impact supplement (comprising five questions) designed to assess the potential burden related to the psychopathology of a child in areas such as home life and academic performance. For this study, we will use only the SDQ impact supplement, in order to assess the burden of the depressive and anxiety symptomatology.ARI—The ARI is a seven-item irritability scale that includes six items related to symptoms related to irritability and one item related to the potential impact of irritability [62]. The ARI has been adapted for use in Brazil [45].TSQ [48]—Parental satisfaction with the telepsychotherapy sessions will be assessed (in the intervention group only) with an adapted version of the TSQ [48]. It is a 14-item questionnaire that assesses parameters such as difficulties in contacting the therapist and willingness to use telemedicine services again.EMA of emotional problems—We will deliver an ESM protocol to assess mood, stress and emotion (Table 1). The protocol will be delivered using the COMVC application, which will send notifications for participants to rate affirmations about their current state (e.g. “Right now, I feel happy”) using an 8-point Likert scale with responses ranging from “not at all” to “very much”. It represents a brief version of the ESM protocol used in the Remote Assessment of Disease and Relapse in Major Depressive Disorder study [47], a prospective multicenter study to determine the usability, acceptability and feasibility of remote collection of data regarding the symptoms of depression.pRMT—The pRMT application, from the RADAR-base platform [47], will be used in order to monitor the following smartphone features: the position sensor, which allows the relative location to be registered by using data on latitude and longitude; the movement sensors (accelerometer, gyroscope and magnetometer), which allow movement to be registered by measuring acceleration, rotation and the raw magnetic field, as well as by counting steps; environmental (light) sensors, which register the level ambient light; and activity logs, which include the time spent using the smartphone in general and on specific applications, as well as battery level and nearby Bluetooth-enabled devices.

**Table 1 Tab1:** Ecological momentary assessment protocol

“We would like to know how you are feeling right now”								
	**0 (not at all)**	**1**	**2**	**3**	**4**	**5**	**6**	**7 (very much)**
1. I sleep well								
2. I feel cheerful								
3. I feel down								
4. I feel anxious								
5. I feel relaxed								
6. I feel irritated								
7.I feel stressed								
8. I feel content								
9. I feel insecure								
10. I feel hopeful								
11. I feel lonely								
12. I am satisfied with myself								
13. I feel restless								
14. I feel self-confident								
15. Overall, I feel well								
16. I am ruminating								
17. I am able to concentrate well								

### Plans to promote participant retention and complete follow-up {18b}

If a participant in the intervention group misses a session, the therapist will try to reschedule it, respecting two conditions: there should be at least 48 h between sessions (so that participants can have enough time to do the “homework tasks”), and there should be no more than 4 weeks between the date of the first scheduled session and that of the last scheduled session. If the sessions cannot be rescheduled according to those conditions, the first four sessions will be prioritised, given that the fifth session is expected to be mostly a revision session. Participants will complete outcome assessments at T1 and T2, irrespective of the number of sessions completed or videos watched.

### Data management {19}

All data from the assessments and the sessions will be entered in the Research Electronic Data Capture [63], which is a secure database. The clinical data collected in the enrolment phase will be confirmed or corrected in the baseline assessment. All data, except the sociodemographic data, the TSQ score, the EMA results and the passive data, will be collected by a trained assessor.

The self-report data will be stored on the COMVC servers. The mobile smartphone sensor data will be stored on the RADAR-base platform. Both categories of data will also be backed up to Google Drive and Dropbox, and only the research team will have access to them.

### Confidentiality {27}

Information will be collected in a manner that protects the privacy of the participants. Sensitive information that might identify participants (name, hospital record number, telephone, physical address or electronic address) will not be included in the database. Each participant will be assigned an anonymous identifier. Passive data collection will also be conducted in a manner that protects sensitive data. The RADAR-base platform automatically converts information from position sensors (GPS data) into relative location using an unspecified point as a reference. Participant addresses or geographical (absolute) locations will not be registered. Likewise, we will not register the contents of emails and messages, nor the sites or content viewed on the web. Participants may choose not to participate in the EMA and the passive data collection, while still participating in the rest of the study.

### Plans for collection, laboratory evaluation and storage of biological specimens for genetic or molecular analysis in this trial/future use {33}

This trial will not involve the collection of biological specimens.

## Statistical methods

### Statistical methods for primary and secondary outcomes {20a}

We will use generalised linear mixed models (GLMMs) to analyse the effects of the intervention. The primary outcome will be the change, from T0 to T1, in the total scores on the RCADS-25-P and RCADS-25-C. Fixed and random effects will be modelled with GLMMs. The fixed effects will be the randomisation status (intervention group vs. active comparator group) as an independent variable, along with the potential confounders (age, sex and other baseline characteristics). The random effect will be on the subject (first) level. Time will be inserted as a continuous independent variable. We will use the intention-to-treat approach—all randomised subjects will be included in the analysis, even if they drop out or switch arms. The marginal means of the models will be extracted by randomisation status and time, after which they will be plotted in a time series. In a second step, we will analyse the effects that the intervention has on the symptoms of depression and anxiety in the children and adolescents. For all models, we will present the beta coefficients with a confidence interval of 95%. For all statistical tests, the level of significance will be set at 5%. Analyses will be performed with the Stata software package, version 16.0 (StataCorp, College Station, TX, USA), and the programme R, version 4.0.1 (The R Foundation for Statistical Computing, Vienna, Austria).

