### Intervention description {11a}

#### Intervention group

We have developed a brief standardised, manualised cognitive-behavioural intervention for treating anxiety and depression in children and adolescents, to be implemented by trained psychologists via teleconference or telephone call. The main focus of the sessions will be skills training, with a CBT approach that employs vocabulary adapted to the target population. The psychotherapy programme will consist of five structured weekly sessions. The structure of each session is described in detail in the manual. Below is a brief description of the topics covered in each psychotherapy session.Session 1—The initial session covers the following: identification of the main symptoms and problems; psychoeducation on stress responses; strategies for improving communication within the family (e.g. defining minimal routines at home and how parents can listen to their child empathically); and relaxation and mindfulness techniques (diaphragmatic breathing exercises).Session 2—The second session focuses on emotion recognition and anger management. There is a psychoeducational component on emotions, covering the basic emotions of happiness, sadness, fear, disgust, surprise and anger, as well as their usefulness (e.g. motivating us to take necessary actions) and pitfalls (e.g. the potential for suffering). There is a greater emphasis on anger, exploring its physical, cognitive and behavioural components, and on strategies for coping with outbursts of anger, such as how they can be prevented and how to recover from one.Session 3—The third session focuses on behavioural activation, which is a technique based on the idea that avoidance behaviours exacerbate depressive symptoms. The technique is aimed at promoting adaptive behaviours that would be positively reinforced by scheduling potentially enjoyable and meaningful activities [37]. The rationale of behavioural activation is to stimulate participation. The therapist will guide the child/adolescent, with the help of a guardian, in creating a brief list of activities to be performed in the following week.Session 4—The aim of the fourth session is to teach the principles of cognitive restructuring. To that end, there is a psychoeducational component on what “thoughts” are, how to recognise them and the effects they might have on us, covering the basics of the cognitive model developed by Aaron T. Beck [38]. The last part of the session will focus on Socratic questioning [39].Session 5—The final session is aimed at revising any content of the previous sessions that was not clear to the family and providing a referral if necessary (e.g. to the public health care system if the child/adolescent is still symptomatic).

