#### Active control group

Children and adolescents in the active control group will receive a psychoeducational intervention that consists of the same 15 videos described above. The videos will be made available through the same smartphone application and on to the same schedule described for the intervention group.

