### Strategies to improve adherence to interventions {11c}

The intervention sessions will be recorded on video; 10% will be randomly selected to be watched by one of the authors of the manual, to assess therapist adherence to the protocol. Each session is described in detail in the manual, helping make the intervention more homogeneous among the various therapists of the research group. All of the therapists will receive weekly supervisory sessions led by senior psychotherapists. An assessor blinded to the allocation will register the percentage of psychoeducational videos watched by the patient and guardian.

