Our protocol has some limitations. For instance, the active control group intervention is a self-guided psychoeducational activity, which could result in an overestimation of the intervention group results. We will not be comparing the intervention to a therapist-lead intervention to test the specific effects of the implementation procedure. The reportedly high (approximately 30%) dropout rates in trials of psychotherapy interventions [67–70] might be a challenge. The number of sessions (five) might also be insufficient for individuals who are more symptomatic. It is estimated that three quarters of the Brazilian population has internet access, although the level of connectivity is not homogeneous, with some areas lacking stable connections [71]. These factors could therefore limit the access to the intervention to part of the population. However, it is a robust intervention that could help increase the existing evidence in the area of telemedicine and in alternative ways of measuring data, such as via smartphone apps. It also foresees the alternative use of telephone for the intervention, in cases where poor internet connectivity continues to be an issue.

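### The primary model has only a participant random effect, although several therapists treat the intervention arm and none the control arm; if outcomes correlate within therapist, its standard error is too small

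*Protocol article*

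**What the plan says.** **Model.** Statistical methods {20a} names a generalised linear mixed model. Its fixed effects are randomised arm, "along with the potential confounders (age, sex and other baseline characteristics"), and time as a continuous variable. On the random part it says: "The random effect will be on the subject (first) level". Therapist appears in neither part.

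**Delivery in the intervention arm.** The Intervention group section describes five weekly sessions, "to be implemented by trained psychologists via teleconference or telephone call". Strategies to improve adherence {11c} makes clear that there is more than one therapist: the manual is credited with "helping make the intervention more homogeneous among the various therapists of the research group". The same section adds weekly supervision and a fidelity review of 10% of recorded sessions.

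**Delivery in the control arm.** Controls "will receive a psychoeducational intervention that consists of the same 15 videos described above". The Discussion confirms that "the active control group intervention is a self-guided psychoeducational activity".

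**Sample size {14}.** The authors "expect an effect size within the lower bound of that confidence interval, that is, 0.41". The result is: "Therefore, the minimum sample size would be 190 participants, with an alpha of 0.05, power of 80% and 1:1 randomisation". The rise to 280 is attributed to 30% attrition alone.

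**The concern.** Children seen by the same therapist share that therapist's skill, style and adherence to the manual, so their outcomes may be correlated. Where they are, the intervention arm carries less independent information than its head count suggests. Control children have no such grouping.

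This is not a detail left for an analysis plan. The article states the random structure, in the singular and at one level. A random intercept per child cannot absorb correlation between different children.

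At stake are the confidence interval and p-value of the primary comparison. Any error runs one way: the interval is too narrow and the test rejects too often. The Background also says the manual is meant for other professionals across Brazil. For inference reaching beyond the trial's own therapists, variation between therapists belongs in the uncertainty.

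**Working it through.** **Inputs from the protocol article.** Standardised effect 0.41, alpha 0.05, power 80%, 1:1 allocation, minimum 190, attrition 30%, total 280 (all from Sample size {14}). One random effect, at participant level (Statistical methods {20a}). Several therapists in one arm, none in the other.

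**Inputs assumed.** Number of therapists K, equal caseloads, and therapist ICC. The documents give none of these. The main range is K = 8 to 15 and ICC = 0.02 to 0.05, with lower and higher values shown as well.

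**Step 1: reproduce the stated figure.** A two-sided, two-sample t-test with effect 0.41, alpha 0.05 and 80% power needs 94.35 per arm, so 95 per arm and 190 in total. This matches exactly. The normal approximation gives 94 per arm (188). One-sided testing would give 148, so the plan is two-sided. Dividing 190 by 0.70 gives 272, close to the stated 280. Evaluable: 280 × 0.70 = 196, or 98 per arm. No design effect enters, so the sample size treats all children as independent.

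**Step 2: formulas.** With n = 98 per arm and n/K children per therapist:

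- Design effect in the intervention arm: DE = 1 + (98/K − 1) × ICC. In the control arm it is 1.
- True variance divided by the model's variance: R = (1 + DE)/2.
- Share by which the model understates the variance: 1 − 1/R.
- True type I error of the planned test: 2 × [1 − Φ(1.96/√R)].
- Power with the correct standard error: Φ(0.41/√(2R/98) − 1.96). Since √(98/2) = 7, this is Φ(2.87/√R − 1.96).

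Without clustering (R = 1) power is Φ(0.91) = 81.9%; the t-test gives 81.5%.

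**Step 3: results.**

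| K | ICC | DE | R | Understated by | Type I error | Power |
|---|---|---|---|---|---|---|
| 20 | 0.01 | 1.039 | 1.020 | 1.9% | 5.2% | 81.1% |
| 15 | 0.01 | 1.055 | 1.028 | 2.7% | 5.3% | 80.8% |
| 15 | 0.02 | 1.111 | 1.055 | 5.2% | 5.6% | 79.8% |
| 10 | 0.05 | 1.440 | 1.220 | 18.0% | 7.6% | 73.8% |
| 8 | 0.05 | 1.563 | 1.281 | 22.0% | 8.3% | 71.8% |

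Worked case, K = 8 and ICC 0.05: 98/8 = 12.25; DE = 1 + 11.25 × 0.05 = 1.5625; R = 2.5625/2 = 1.281; √R = 1.132. Then 1.96/1.132 = 1.73, giving 8.3%. Power is Φ(2.87/1.132 − 1.96) = Φ(0.575), about 72%.

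**Step 4: check by simulation.** With about 95 per arm and 40,000 trials per setting, an unclustered t-test rejected a true null in 7.5% of trials at 10 therapists and ICC 0.05, and in 10.1% at 5 therapists and ICC 0.05. The formula at 95 per arm gives 7.5% and 10.4%. With ICC 0 the simulated rate stayed at 5.0 to 5.1%.

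**Step 5: a wider range.** At 95 per arm, K from 5 to 20 and ICC from 0.01 to 0.10, type I error runs from 5.2% (20 therapists, ICC 0.01) to 15.5% (5 therapists, ICC 0.10).

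**The case against.** **The size is assumed.** A reader might infer that the standard errors are certainly too small and that the trial's error rate is known to exceed 5%. The documents do not support that. It requires a therapist ICC above zero and caseloads large enough to matter, and they give no number of therapists, caseload or ICC. This objection stands, and the point has to be conditional.

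**The design works against therapist differences.** The programme is standardised and manualised, every family has the same 15 videos, and section {11c} adds supervision and fidelity review. These measures favour the low end of the ICC range, where the effect is small. They do not establish a zero ICC, and they put no term in the model.

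**The power figures are not those of the planned model.** They come from an unadjusted two-group comparison. The plan adjusts for baseline characteristics and analyses change, so both the power and the relevant ICC could differ. The authors also powered on the lower confidence bound, 0.41, rather than the estimate of 0.62. At 0.62, power in the K = 8, ICC 0.05 case is Φ(4.34/1.132 − 1.96), about 97%. That eases the worry about power but leaves type I error untouched.

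**Therapist identity may well be recorded.** A reader might infer that the therapist term could not be fitted because no therapist code is kept. The article does not show this: Data management {19} sends session data to the database, and sessions are video-recorded.

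**The stated objective is efficacy.** Wide use of the manual is a later aim, so generalising beyond these therapists is partly a choice of inference. With about 8 therapists, the therapist variance would also be poorly estimated. Both remarks are fair, but neither justifies a model that sets the therapist variance to zero.

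**Conclusion.** The point holds in conditional form. The article fixes one random effect, at participant level, for a design in which only the intervention arm is grouped by therapist. The sample size rests on the same independence assumption, and nothing elsewhere in the article corrects either.

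Under the main assumptions (8 to 15 therapists, equal caseloads, 98 evaluable intervention children, ICC 0.02 to 0.05), the true variance of the arm effect is about 6 to 28% larger than the model's; put the other way, the model understates it by about 5 to 22%. Type I error is about 5.6 to 8.3%. Power at 0.41 in an unadjusted comparison is about 72 to 80%, against 81 to 82% without clustering. With an ICC of 0.01 and 15 or more therapists the consequence is negligible. The sponsor should make the change: the structural gap is definite, its size is uncertain and probably moderate, and the remedy needs no change to trial conduct.

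**What to change.** - In Statistical methods {20a}, specify a partially nested model: keep the participant random effect and add a therapist random effect that acts only in the intervention arm, with each control child treated as a cluster of one. Use Satterthwaite or Kenward-Roger degrees of freedom, because therapists are likely to be few.
- Make sure therapist identity is available in the analysis dataset.
- In Sample size {14}, restate the power for the actual number of therapists over a stated ICC range.

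**Cost.** A revised model statement and confirmation of one data field; randomisation, visits and participant burden do not change. The interval will be wider and the stated power lower, more so if therapists are few. The small-sample degrees of freedom would lower power further, and the figures above do not include that loss. If the ICC proves close to zero, the cost is small.

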### Eligibility criteria {10}

Children and adolescents with the following characteristics will be eligible to participate in the study: being between 8 and 17 years of age; living in Brazil; having a total *t*-score of ≥ 70 on the 25-item version of the Revised Children’s Anxiety and Depression Scale, parent report (RCADS-25-P) [28]; and having a total *t*-score ≥ 70 on the RCADS-25, child report (RCADS-25-C) [29]. The RCADS-25 measures the frequency of symptoms of anxiety and depression, using a 4-point Likert scale (“never”, “sometimes”, “often” or “always”), with subscale scores (for anxiety and depression, respectively) and an overall score. In an international consensus, the RCADS-25 was recommended as an outcome measure for anxiety and depression symptomatology in children and adolescents [30].

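### With a single subject-level random effect, the T ≥ 70 entry cut and 30% loss, the standard error of the T0–T1 contrast can be wrong, usually too small

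*Protocol article*

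**What the plan says.** All references are to the protocol article.

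- **Statistical methods for primary and secondary outcomes {20a}.** The primary outcome is the T0–T1 change in the total RCADS-25-P and RCADS-25-C scores, analysed by GLMM. On the covariance the section says only: "The random effect will be on the subject (first) level". Time enters as a continuous variable, every randomised child is kept, and marginal means are taken by arm and time. On the test level: "For all statistical tests, the level of significance will be set at 5" per cent.
- **Eligibility criteria {10}.** The total on the parent form must be a "score of ≥ 70 on the 25-item version", and the child form carries the same rule: "having a total *t*-score ≥ 70 on the RCADS-25, child report (RCADS-25-C". Under Participant timeline {13}, these criteria are checked at the videoconference that supplies the T0 scores.
- **Sample size {14}.** "the minimum sample size would be 190 participants, with an alpha of 0.05, power of 80% and 1:1 randomisation", and then "Assuming an estimated attrition rate of 30%, we will need a total sample of 280 participants".

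The article gives no SD, no between-visit correlation and no residual variance structure. It does not say whether T2 is in the primary model, and it names no group-by-time term.

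**The concern.** A lone random intercept with equal residual variance implies that RCADS-25 has the same variance at T0, T1 and T2 and the same correlation for each pair of visits. Selection on T0 makes this implausible: T0 is cut off from below, while T1 and T2 are free to spread. The cut also lowers the correlation of T0 with later visits more than it lowers the T1–T2 correlation.

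Children lost after T0 still contribute their T0 score. The model pools the narrow T0 variance with the wider T1 variance and weights those T0 scores accordingly. If the resulting standard error is too small, the primary confidence interval is too narrow and the test does not hold its stated 5% level.

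**Working it through.** **1. The plan's own figures.** With "expect an effect size within the lower bound of that confidence interval, that is, 0.41": n per arm = 2(1.96 + 0.84)²/0.41² ≈ 93.4, so 94 per arm (188). The t-test version gives 95 per arm, 190 in total. 190/0.70 = 271.4, so 272, which the plan takes up to 280. These figures reproduce. Below, n = 140 per arm and p = 0.70 are observed at T1.

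**2. Two visits, arm-by-time contrast.** Let the true T0 variance, T1 variance and covariance be a, b and c. Let v and ρ be the single variance and correlation that the random-intercept model converges to; they minimise p[log|W| + tr(W⁻¹V)] + (1−p)[log v + a/v], where V is the true covariance matrix and W = v[1 ρ; ρ 1]. Put k = ρ + (1−ρ)p. Per arm, the variance of the estimated mean change is

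- true: (b − 2kc + k²a)/(np) + (1−k)²a/(n(1−p))
- claimed by the model: v(1 − 2kρ + k²)/(np) + (1−k)²v/(n(1−p))

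The actual size is 2[1 − Φ(1.96 × model SE/true SE)].

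*Example (assumed values after selection):* SD 6 at T0, SD 10 at T1, correlation 0.5, so a = 36, b = 100, c = 30. The fit gives v = 61.58, ρ = 0.4135, k = 0.8241.
- True: 75.00/98 + 0.03095 × 36/42 = 0.7653 + 0.0265 = 0.7919 per arm; SE of the difference √(2 × 0.7919) = 1.258.
- Model: 61.43/98 + 0.03095 × 61.58/42 = 0.6268 + 0.0454 = 0.6722 per arm; SE √(2 × 0.6722) = 1.159.
- Ratio 0.921; size 2[1 − Φ(1.806)] = 7.1%.

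By T0/T1 SD ratio: 1.0 gives 5.0%, 0.8 gives 5.9%, 0.6 gives 7.1%, 0.4 gives 8.5%.

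*No loss:* k = 1. The model claims 2v(1−ρ)/n and the truth is (a + b − 2c)/n. The fit sets v = (a+b)/2 and vρ = c, so the two are equal and the size is exactly 5.0%.

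**3. Four scenarios.** Assumed before selection: mean 62, SD 12, parent–child correlation 0.4, and the T0–T1/T0–T2/T1–T2 correlations shown. Cases are kept if both T0 scores are ≥ 70. After selection the SD is about 6.5 at T0 and 9.7–10.9 at T1. Large-sample sizes with the entry cut and 30% lost after T0 (linear time at 0, 5 and 9 weeks):

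| Correlations | T0, T1 only | Three visits, categorical | Three visits, linear |
|---|---|---|---|
| .7/.7/.7 | 6.7% | 5.9% | 5.8% |
| .6/.55/.8 | 6.9% | 7.8% | 10.1% |
| .5/.45/.75 | 7.2% | 7.9% | 9.9% |
| .5/.45/.85 | 7.2% | 9.2% | 11.7% |

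REML simulation of the categorical model (4,000 runs, about 25–30% missing) agrees: 6.0%, 7.8%, 8.0% and 9.0%, with mean SE against empirical SD of 1.181/1.228, 1.240/1.380, 1.348/1.506 and 1.294/1.505, that is 4–14% too small. T1 ANCOVA on the same data gave 5.0%.

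**4. Where the three-visit excess comes from** (categorical time, same scenario order):

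| | Size |
|---|---|
| no cut, no loss | 5.0, 6.7, 6.8, 8.0% |
| cut, no loss | 4.6, 6.4, 6.4, 7.7% |
| no cut, 30% loss | 5.0, 6.6, 6.7, 7.8% |
| cut and 30% loss | 5.9, 7.8, 7.9, 9.2% |

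In the last three scenarios, 1.7–3.0 of the 2.8–4.2 points above 5% are present without either design feature. They come from setting the T1–T2 correlation above the T0–T1 correlation. Cut and loss together add 1.1–1.2 points. With equal correlations they account for the whole 0.9.

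**5. Wider assumptions** (SD 10, mean 50–75, correlation 0.3–0.85 before selection).
- Two visits, 30% loss: 5.5–8.8% in large samples; 6.0–9.4% in simulation.
- Three visits, equal correlations: 2.5–5.6% with linear time and about 4–6.6% with categorical time.
- Three visits, linear time, correlations that decay over time: 8–11%.
- Arm as a main effect only: 4.9–5.0%.

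**The case against.** The strongest reply is that the article states only where the random effect sits. Equal residual variance is a software default, not a commitment. Visit-specific variances or robust standard errors would be compatible with the sentence, and covariance structure and degrees of freedom are normally settled in a SAP. This stands in part: the point applies to a literal fit. But the article does state the random structure, and a SAP that carried it over unchanged would inherit the problem.

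It can also be said that the only treatment term named is the arm main effect, whose test holds its level. That is correct, but the main effect averages over T0, before treatment, and so does not test the T0–T1 change that is declared primary.

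The 30% is a planning allowance, and under {18b} children are assessed at T1 and T2 whatever their attendance. With less loss the two-visit error shrinks, to nothing at zero loss.

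A reader might infer that the planned test simply runs at 6–9% because of the entry rule. The documents do not support that. They give no SDs or correlations, do not fix the visits or the contrast, and some readings are conservative. A reader might also infer that a T1–T2 RCADS-25 comparison is distorted. None is planned (the outcomes section {12} compares T0 with T1 and T0 with T2) and none was calculated.

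**Conclusion.** The concern holds conditionally. It requires a random intercept with equal residual variance, a group-by-time test of the T0–T1 change, a T0 variance narrowed by the entry rule, and loss near the planned 30% with T0-only children retained. The standard error can then be wrong, usually too small.

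Under the assumed scenarios the 5% test runs at 6.7–7.2% with T0 and T1 only (roughly 5.5–9% over wider assumptions), about 6–9% with three categorical visits, and about 6–12% with linear time. With three visits and equal correlations it is about 6% or less in most settings (6.6% at most) and can be conservative. Much of the three-visit excess reflects unequal correlations, which would trouble this model without any entry threshold. The direction is reasonably firm for the two-visit model; the size rests on SDs and correlations that are not in the documents. It is worth correcting before analysis, with medium confidence in the magnitude.

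**What to change.** For RCADS-25, replace the sentences on the random effect and on continuous time with: *T-scores at T0, T1 and T2 will be modelled with visit as a categorical factor, arm-by-visit terms and an unstructured residual covariance over visits (REML, Kenward-Roger degrees of freedom). The primary test is the arm contrast for the T0–T1 change. If the model does not converge, T1 will be analysed by ANCOVA adjusted for T0 with robust standard errors.*

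The unstructured model removes both the common-variance and the equal-correlation assumption, so it should target 5% under loss at random whichever correlation pattern occurs. That follows from theory and was not simulated here; the ANCOVA fallback was simulated and held 5%.

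The cost is a few lines of text. Three visits need six covariance parameters, easily estimated from 280 children, and both named packages can fit the model. Where the old standard error was too small, the interval will be somewhat wider. The same structure could be used for the other scales measured at all three visits, but that is optional: entry is not cut on them and no effect was quantified.
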